## Abstract

**Background:**

Depression is one of the most frequent and severe psychiatric conditions. Many chemical drugs to treat depression are associated with adverse reactions and have shortcomings. Traditional Chinese medicine is of great significance in the prevention and treatment of depression. Xiaoyao pills has achieved good results in clinical application, which has the advantages of quick effect and no obvious adverse reactions. The aim of our study is to evaluate the efficacy and safety of Xiaoyao pills on mild to moderate depression patients.

**Methods:**

This study is a multi-centre, double-blinded, randomized and placebo-controlled clinical trial. A total of 108 participants are assigned to three groups: Xiaoyao pill group taking Xiaoyao pills twice daily for 4 weeks, placebo group taking placebos twice daily for 4 weeks and normal group without taking any drug. The primary and secondary outcome measures are the Hamilton Depression Scale (HAMD) and Traditional Chinese Medicine (TCM) Syndrome Scale. The assessment is at baseline (before treatment initiation), 1 week, 2 weeks 4 weeks after the first treatment. Exploratory outcome is also assessed to explore the mechanism of Xiaoyao pills at baseline and 4 weeks.

**Discussion:**

The results from this study will provide clinical evidence on the efficacy and safety of Xiaoyao pills in patients with mild to moderate depression with syndrome of liver stagnation and spleen deficiency.

**Trial registration:**

ClinicalTrials.gov ISRCTN12746343. Registered on September 25, 2020.

## Introduction

### Background and rationale {6a}

Depression is one of the most frequent and severe psychiatric conditions, with an estimated prevalence reaching 15% in the general population [1]. Depression is characterized by sadness, loss of interest and pleasure, feelings of guilt, feeling of worthlessness, low appetite, fatigue, and poor concentration [2]. Depression is known to dramatically increase the risk of premature death by suicide or other general medical conditions, such as vascular diseases [1]. Considering the alarming impact of COVID-19 infection on mental health [3, 4], we should pay more attention to the treatment of depression. There are many treatments, including pharmacological, psychological, and neurostimulatory options that are associated with remission of symptoms and full restoration of psychosocial function. Unfortunately, a significant proportion of patients do not achieve sustained remission, despite serial treatments [5]. Clinical practice has proven that many chemical drugs have beneficial therapeutic effects in depression, but they are also associated with adverse reactions, such as drowsiness and dystonia, and have shortcomings, such as a narrow antidepressant spectrum and a high rate of relapse [6].

### Objectives {7}

This study intends to carry out a multi-center randomized controlled and double-blind trial to observe the efficacy of Xiaoyao pills in the treatment of mild to moderate depression.

### Trial design {8}

This study is a multi-center, double-blinded, randomized, placebo-controlled, parallel group and exploratory clinical trial with allocation radio 1:1. The trial protocol has been approved by the ethical committee of the Beijing University of Traditional Chinese Medicine (ref: 2020BZYLL0304) and is registered with ISRCTN at Current Controlled Trials (ISRCTN 12746343). The patients are provided with written informed consent. The trial is based on the principles of ICH-GCP [15] and appropriate legal regulations for recommended items to address in a clinical trial protocol according to the SPIRIT 2013 Checklist [16] and the Consolidated Standards of Reporting Trials (CONSORT) statement [17].

## Methods: participants, interventions, and outcomes

### Study setting {9}

#### Study setting and participants

A total number of 72 participants with mild-to-moderate depression (referred to symptoms of liver stagnation and spleen deficiency) and 36 healthy participants are recruited at the five trial sites in china, including Peking University Sixth Hospital, the First Affiliated Hospital of Jinan University (Guangzhou Overseas Chinese Hospital), the Affiliated Brain Hospital of Guangzhou Medical University, Dongfang Hospital (Beijing University of Chinese Medicine Second Affiliated Hospital), and Beijing Anding Hospital Capital Medical University. Participants are informed of details about the study which are purpose, duration, procedures, and key contacts, as well as risks and potential benefits. Participants may withdraw their consent for any reason without any consequences at any time. Eligible 72 participants with mild-to-moderate depression are randomly allocated to Xiaoyao pill group (Group 1) and placebo group (Group 2), who are required to take Xiaoyao pills and placebos, respectively, twice daily for four consecutive weeks. 36 healthy participants are allocated to the normal group (Group 3) without taking any drug. The flow chart is listed in Fig. 1.

**Fig. 1 Fig1:**
[figure not shown]
Study sequence

### Eligibility criteria {10}

#### Inclusion criteria

Participants meeting the following criteria are included:

1. Meet the Diagnostic Statistics Manual of Mental Disorders (DSM-5) regarding the diagnosis of mild to moderate depression;

2. A score between 20 and 35 on Hamilton Depression Scale (HAMD);

3. Meet the TCM criteria of liver stagnation and spleen deficiency syndrome;

4. Aged between 16 and 18 years old;

5. Patients agree to participate in this trial and assign the informed consent;

6. Capable of reading and follow-up treatment, and permanently live locally.

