### Outcomes {12}

#### Primary outcome measures

##### Hamilton Depression Scale (HAMD)

The HAMD is a tool developed for clinical evaluation of depression and is widely used in studies [18]. It is composed of 17 questions. Each question is scored from 1 to 4 points, where a higher score indicates severe symptoms; 0 to 7 point is normal, 7 to 17 points may have depression, 17 to 24 points definitely have depression, and more than 24 points means severe depression. Measurements are taken at the baseline, 1 week, 2 weeks, and 4 weeks after treatment.

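### The HAMD entry window of 20 to 35 runs 11 points into the protocol's own severe band although the trial is confined to mild to moderate depression, and the stated item scoring cannot produce the scale's lowest bands

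*Protocol article*

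**What the plan says.** The protocol article names its population consistently. The Objectives section says the trial will "observe the efficacy of Xiaoyao pills in the treatment of mild to moderate depression". Study setting and participants states "Eligible 72 participants with mild-to-moderate depression are randomly allocated to Xiaoyao pill group (Group 1) and placebo group (Group 2"). The Discussion gives as a limitation that only mild to moderate cases are recruited.

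The Inclusion criteria apply two severity conditions together. Item 1 is a DSM-5 criterion "regarding the diagnosis of mild to moderate depression". Item 2 is "A score between 20 and 35 on Hamilton Depression Scale (HAMD").

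Under Primary outcome measures the HAMD is described once: "It is composed of 17 questions", and "Each question is scored from 1 to 4 points, where a higher score indicates severe symptoms". The bands are 0 to 7 for normal and 7 to 17 for possible depression, and then "17 to 24 points definitely have depression, and more than 24 points means severe depression". No band is labelled mild or moderate, and no other version of the scale is described.

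**The concern.** Two severity rules in one list of inclusion criteria point to different populations once the outcome section's bands are applied. Item 1 restricts entry to mild to moderate disease, while item 2 admits totals that the protocol elsewhere calls severe. Sites at five centres would have to decide which prevails.

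Three other parts of the protocol raise the stakes:

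- The Rejection criteria call for removal of enrolled cases that were wrongly diagnosed and included. A randomised patient with a HAMD of 28 satisfies item 2 but is severe by the outcome bands. Whether that patient stays could become a judgement made after randomisation, in a trial of 72 patients.
- The section on additional analyses rules out subgroups by mild or moderate depression, so no planned analysis would show to which severity the result applies.
- The Abstract promises evidence for mild to moderate depression. That claim depends on who is let in.

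The scoring sentence is a second, separate problem. It is the stated scoring rule of the primary outcome, and it does not fit the bands printed beside it. The data-collection section says that the EDC system checks entry ranges. If those limits followed the sentence as written, item scores of zero would be refused.

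**Working it through.** **Inputs, all from the protocol article**

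- Entry window: 20 to 35 (Inclusion criteria, item 2).
- Number of items: 17; item score: 1 to 4 (Primary outcome measures).
- Bands: 0 to 7, 7 to 17, 17 to 24, above 24 (same section).
- Named population: mild to moderate (Objectives; Study setting; Inclusion criteria, item 1; Discussion).

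**Step 1. Can the scale's stated lower end be reproduced?** The bands start at 0.

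- Lowest total = 17 × 1 = 17.
- Highest total = 17 × 4 = 68.

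The stated scoring gives 17 to 68, so a total of 0 is not reproduced. With an item floor of 0, which is an assumption and not in the document, the range is 0 to 68 and every band can be reached.

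**Step 2. Scores admitted by the window, ends included.**

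- Admissible whole numbers: 35 − 20 + 1 = 16.
- Above 24: 35 − 25 + 1 = 11, and 11/16 = 68.75%.
- In 17 to 24: 20 to 24, which is 5 values.
- In 7 to 17: none.

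With the ends excluded (21 to 34) there are 14 values, of which 10 (25 to 34) are above 24. The finding does not depend on how the ends are read.

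**Step 3. Each band against the window and against the 1-to-4 scoring.**

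| Band | Values in band | Admitted by 20 to 35 | Reachable with items 1 to 4 |
|---|---|---|---|
| 0 to 7 | 8 | 0 | 0 |
| 7 to 17 | 11 | 0 | 1 (17 only) |
| 17 to 24 | 8 | 5 | 8 |
| above 24 (25 to 68) | 44 | 11 | 44 |

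The window omits all of 7 to 17, and also 17 to 19 from the next band. The scoring rule blocks 0 to 7 and 7 to 16. All 16 scores in the entry window can be reached. The scores 7 and 17 each belong to two bands.

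**Step 4. The two inclusion items together.** If the DSM-5 criterion screens out everyone whom the HAMD bands call severe, the values 25 to 35 never operate and the effective window is 20 to 24. If it does not, patients called severe by the primary outcome scale are randomised as mild to moderate. The text does not say which is meant.

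**The case against.** The strongest reply is that the criteria are cumulative. A high HAMD total qualifies nobody alone: the patient must also have a DSM-5 diagnosis of mild to moderate depression, and the exclusion criteria remove severe suicidal risk, treatment-resistant depression and obvious psychotic symptoms. This stands in part. It means that the trial could admit patients its scale calls severe, not that it will. It does not make items 1 and 2 agree with the bands.

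A reader might also infer more than the document supports:

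- That all mild depression is excluded. No band is labelled mild. Only if mild were equated with 7 to 17, or with totals below 20, would that follow. If mild reaches into 20 to 24, some mild cases remain eligible.
- That about 69% of patients would be severe. The figure counts score values. The document gives no HAMD distribution.
- That the scoring rule makes the whole scale, or the entry window, unreachable. It blocks only totals below 17.
- That change scores would be wrong. If every item moved up by one point, the shift would cancel in a change from baseline. If only zeros became ones, the effect would depend on item data that are not given. The statistical methods mention a cure rate, but nothing ties it to these bands.

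The phrase on item scoring may well be a slip of description, since the protocol requires a unified form at all centres and cites a source for the scale. That lowers its weight. It is still the stated rule for the primary outcome.

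**Conclusion.** The point holds as an internal contradiction. The entry window extends 11 points into the band that the protocol calls severe (11 of 16 admissible scores, or 10 of 14 with the ends excluded), and it omits the 7 to 17 band and 17 to 19. The named population is mild to moderate throughout. The DSM-5 criterion may soften the practical effect but leaves the conflict in place.

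The scoring description is a second, smaller error. As written, totals start at 17, so the normal band and 7 to 16 cannot occur, and two cut-offs fall in two bands each.

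The conclusion assumes whole-number totals and that the window and the bands refer to the same 17-item scale, the only one described. How many severe patients would enter, and whether mild cases are lost, cannot be determined from the document.

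**What to change.** - Reconcile the Inclusion criteria and the HAMD description with the Objectives, Study setting and Discussion, so that the window, the severity bands and the population named in the conclusions agree. State which bands count as mild and which as moderate, and how the DSM-5 and HAMD conditions work together. Which cut-off is right is for the investigators and the sponsor.
- Correct the sentence "Each question is scored from 1 to 4 points" so that the stated bands can be reached, and remove the overlaps at 7 and 17. Check the EDC range limits against the corrected text.
- Keep patients already randomised under the current window in the analysis, and reword the removal rule in the Rejection criteria so that it does not contradict this. Report how many had a baseline HAMD above 24.

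The cost is one amendment to the eligibility and outcome wording, with the ethics approval and notices that the protocol requires for amendments, and one EDC check. If the window is moved or narrowed, the recruitment rate may change. Recruitment is already under way, so delay adds patients entered under unclear criteria.

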#### Who will take informed consent? {26a}

All participants with depression enrolled in the study as well as 36 healthy people sign a paper version of informed consent prior to study initiation. The recruitment of participants in each study centre is made by the researchers (doctors) in each study center. Researchers make face-to-face evaluation of patients or healthy people who are willing to participate in the project. If the participants meet inclusion criteria, the researchers inform them to sign the informed consent. Only after signing the informed consent can the trial process be officially started. Two copies of the informed consent were kept by the researchers and the participants, respectively.

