## Discussion

Depression is a common affective mental disorder, which is associated with a high burden of disease. Research suggests that chronic diseases, genetic factors, social, and environmental factors can induce depression [22]. The common therapy for depression is antidepressants. Due to the side effects of drugs for depression, the compliance of patients is rather poor and then affect the drug efficacy [23]. Therefore, it is urgent to find safe and no side-effect treatment. A number of patients with depression would prefer traditional Chinese medicine over pharmacotherapy when our study demonstrates the effectiveness and safety of traditional Chinese medicine to treat depression. This will be especially relevant for patients who do not respond to medical therapy or who experience adverse side effects to drug therapy.

According to traditional Chinese medicine theory, liver stagnation and spleen deficiency syndrome is one of the main syndromes of depression. Especially due to people’s unhealthy eating habits and long-term emotional stress from life and work in modern society, the symptoms of the liver stagnation and spleen deficiency are very common. In clinical practice, the syndrome of liver stagnation and spleen deficiency has become a high incidence and common syndrome. Xiaoyao pills has good effect of soothing the stagnated liver and strengthening the spleen. In our study, TCM syndrome efficacy evaluation is added in order to determine more suitable patient populations to take Xiaoyao pills and optimize indications.

The potential mechanism of Xiaoyao pills to treat depression mainly focused on animal experiments [24–28]. There is little evidence about the potential mechanism about Xiaoyao pills to treat depression in clinical studies. Therefore, in addition to the efficacy evaluation of Xiaoyao pills, the action mechanism of Xiaoyao pills from the perspective of transcriptomics and DNA methylation sequencing will also be studied in our trial.

However, our study has limitation. The limitation concerns the fact that we will only recruit mild to moderate depression patients with syndrome of liver stagnation and spleen deficiency in order to ensure the curative effect. Effectiveness of TCM for different types of depression is not evaluated.

Therefore, a clinical trial about traditional Chinese medicine to treat different types of depression are still needed.

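### The only age criterion, 16 to 18 years, does not fit the age-unrestricted patient population described in the rest of the protocol article

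*Protocol article*

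**What the plan says.** Under Eligibility criteria {10}, item 4 of the Inclusion criteria reads "Aged between 16 and 18 years old". No other section gives an age limit, and age does not appear among the Exclusion criteria.

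The population is described elsewhere without reference to age. Objectives {7} states the aim as "to observe the efficacy of Xiaoyao pills in the treatment of mild to moderate depression". The Background and Discussion paragraphs of the abstract speak of patients with mild to moderate depression, the latter adding the TCM syndrome. Recruitment {15} relies on posters in centres and communities, social-media articles that anyone can read, and outpatient clinics. In the Discussion, the target syndrome is said to be common partly because of "long-term emotional stress from life and work in modern society", and the one limitation given is: "The limitation concerns the fact that we will only recruit mild to moderate depression patients with syndrome of liver stagnation and spleen deficiency".

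On consent, item 5 of the Inclusion criteria reads "Patients agree to participate in this trial and assign the informed consent". Section {26a} says "All participants with depression enrolled in the study as well as 36 healthy people sign a paper version of informed consent prior to study initiation" and "Two copies of the informed consent were kept by the researchers and the participants, respectively".

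**The concern.** An age window of 16 to 18 would make this an adolescent trial, yet nothing else in the article treats it as one. Either the printed range is wrong, or the range is right and the objective and conclusions are too broad.

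Eligibility rules fix both the people who may be randomised and the people to whom the estimate applies. Section {26a} makes the rule a gate: "If the participants meet inclusion criteria, the researchers inform them to sign the informed consent". Trial status says recruitment is under way, so the uncertainty bears on current enrolment and not only on later reporting. In a trial with 72 randomised patients, a dispute over whether some of them belong in the analysis could matter to the result.

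**Working it through.** No arithmetic applies. The Sample size {14} paragraph is built from efficacy rates of 32.7% and 91.4%, α = 0.05, β = 0.1 and 15% dropout. Age is not an input, so none of these figures changes with the age range. The check is a comparison of sections.

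**1. Is there a second age range?** No. Item 4 is the only one, so a reader of the article has no other text to follow. The conflict is therefore with sections that set no age limit, not with a rival range.

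**2. Does any other section fit a trial in 16- to 18-year-olds?**

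- Abstract and Objectives {7}: patients are defined by diagnosis and severity, with the syndrome added in the abstract's Discussion paragraph. Adolescents are not mentioned.
- Recruitment {15}: the channels address the public at large. None is specific to young people.
- Concomitant care {11d}, item 3: advice is given for people with high blood pressure, heart disease and diabetes, which sits oddly with such a narrow young age band.
- Discussion, rationale: stress from life and work is cited.
- Discussion, limitation: severity and syndrome are listed, age is not. This is the most telling item. A three-year age band would restrict generalisability at least as much as the syndrome does, and it would be hard to overlook when listing limitations.

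**3. What follows under each reading?**

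- *Rule followed.* All 72 randomised patients are 16 to 18. The conclusions in the abstract and Discussion, which carry no age limit, then extend to adults on whom there are no data.
- *Rule not followed.* Each participant aged 19 or over fails item 4. The Rejection criteria ({11b}) then come into play, and they do not settle the matter. Item 1 couples misdiagnosis with wrongful inclusion by an 'and'. Item 2 concerns the exclusion criteria, which do not include age. The closing sentence keeps the records of rejected cases for efficacy analysis. A correctly diagnosed 25-year-old could be argued in or out.

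**4. How many participants are affected?** The article reports no ages. The bounds are 0 and 72 of the randomised patients, and nothing in the article narrows them.

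**5. Consent.** The criterion admits 16- and 17-year-olds. The consent text names participants as signatories, with copies to researchers and participants. No guardian or assent step appears. Whether one is needed depends on the age of majority, which the article does not give.

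**The case against.** The strongest reply is that there is no direct contradiction. Objectives and conclusions often do not repeat eligibility limits, open advertising does not widen eligibility because each candidate is still screened, and the remark about work stress explains why the syndrome is common without describing the sample. The article also condenses a fuller version 3 protocol, which is what sites would work from, so the printed range may be a slip in the article alone. Much of this stands. The inference rests on silence about age and on an omitted limitation, and the full protocol may already be correct. It does not remove the point: the published rule is explicit, it is the only one, and the intended range cannot be recovered from the article.

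Four stronger readings are tempting, and the document does not support them.

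- *That the trial claims to represent the general population.* That phrase is used only for background prevalence. The trial's stated population is patients with mild to moderate depression and the syndrome.
- *That every adult would have to be removed.* The Rejection criteria are too loosely worded to require this, and an 18-year-old is eligible on the printed range in any case.
- *That most of the 72 are affected.* No ages are reported.
- *That minors are enrolled without guardian consent.* The text says that participants sign, not that they alone sign. The consent pages are not available for review, and an article may leave assent detail to the full protocol.

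**Conclusion.** The point holds as an inconsistency in an operative eligibility rule. The printed range of 16 to 18 years does not fit the population in the abstract, objective, recruitment plan and stated limitation. Either the range is wrong or the conclusions are too broad. A misprint is the more likely explanation, but that is a judgement and not something the article shows.

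The size cannot be stated more closely than between none and all of the 72 randomised patients, because enrolled ages are not given. No sample-size or power figure is affected. The consent element is conditional: it matters only if people below the age of majority are meant to be eligible, and treating 16- and 17-year-olds as minors assumes majority at 18.

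**What to change.** Compare item 4 with the ethics-approved protocol, the registry entry and the age limits set in the EDC, and correct whichever is wrong.

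- If 16 to 18 is intended, restrict the objective and the conclusions to that age group, and add age to the limitation in the Discussion.
- If it is not intended, correct the printed range. Treat participants aged 19 or over who are already enrolled as eligible only if the approved range covered them when they were enrolled. A range widened afterwards would not make them so.
- In either case, if people under the age of majority remain eligible, state in {26a} who consents for them.

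The cost is small: a one-line correction to the article if the approved protocol is already right, or an amendment by the route in {25} if it is not, plus a check of the EDC limits. It should be done before unblinding, so that decisions on who is eligible cannot be influenced by the results.
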